#### Sample size considerations

Based on preliminary studies using the same database and similar inclusion criteria, [4] we expect approximately 80,000 sepsis patients per year between 2016–2019. During the pandemic, the number of Non-Covid-19 sepsis patients may be lower, [16] but due to the inclusion of Covid-19 patients with organ dysfunction, we expect a similar number of patients to be included in our cohort in 2020. Patients with AOK insurance can receive treatment in any acute care hospital in Germany. According to a preliminary analysis, AOK-insured sepsis patients were treated in around 1650 hospitals of the 1900 German acute care hospitals between 2016–2020, thus our study will cover a large majority of German hospitals.

#### Measurements

The module focuses on the three main points of the treatment pathway for sepsis patients: (A) pre-hospital care, (B) inpatient care, and (C) post-acute care.(A)Pre-hospital care: Pre-hospital health care utilization of patients with community-acquired sepsis in the 30 and 7 days prior to hospital admission is assessed. Specifically, contacts with the outpatient care system are analyzed, for example, how often the general practitioner, any outpatient specialist or the statutory health insurance emergency service were consulted, what laboratory or Point of Care Testing (POCT) diagnostics were performed, and if any initial anti-infective therapy was prescribed. For these outpatient contacts, the time latency between the last contact and the following inpatient admission with sepsis is assessed. Furthermore, we analyze which proportion of sepsis patients had pre-sepsis hospitalizations or emergency department visits, as well as which proportion of sepsis patients was admitted as emergency to their index treatment, and for which admission diagnosis.(B)Inpatient care: For the index hospitalization, we assess treatment characteristics, e.g. which organ replacement therapies were conducted, if patients received any immune absorbent therapy, if an intensive care complex or palliative care treatment was administered; as well as the departments involved in sepsis care. We identify inter-hospital transfers and characterize hospitals involved in the chain of sepsis care by the following key characteristics: type of hospital ownership (owned by local or federal state authorities, private for-profit organizations, or by voluntary charitable organizations or churches) number of hospital cases and beds, region (urban/rural), number of cases with (complex) intensive care complex treatment.(C)Post-acute care: Post-acute care utilization is assessed starting at the day of discharge from the last interhospital-transfer from the index hospitalization. We analyze long-term mortality, rehospitalizations (in general, for infectious diseases or recurring sepsis, for vaccine-preventable diseases, for ambulatory-care sensitive diagnosis), emergency department visits in hospitals or treatment by emergency services of the statutory health insurance emergency service, inpatient rehabilitation therapies, utilization of medical remedies, as well as outpatient consultations. We put special emphasis on the out-of-hospital intensive care and the conduction of long-term mechanical ventilation in that setting. Furthermore, psychotherapy and psychiatric medications are recorded and parameters concerning the return to work. Based on a detailed description of this post-acute sepsis care, we attempt to identify classes of health care utilization among sepsis survivors, examine whether such classes are constant or variable over time, and whether specific patient, sepsis, and treatment characteristics are associated with class membership.

For (A), (B) and (C), we examine health care costs from a payer perspective. All analyses will be conducted for the complete cohort of sepsis patients as well as for relevant subgroups, e.g. for patients stratified by age, sepsis focus, underlying pathogen (Covid-19 vs. Influenza vs. others), severity, region, underlying comorbidity, or patients with/without new impairments post-sepsis.

#### Statistical analyses

We present descriptive analyses to describe the extent of health care utilization of different health services after sepsis and use visualization methods to map health care pathways among survivors, such as Sankey diagrams. Sankey diagrams are used to visualize patients’ pathways in terms of provider contacts after the sepsis event. This presentation allows us to detect patient flows after a hospital visit and provides support to define more detailed research questions [17]. Associations between hospital characteristics involved in the chain of hospital care and acute and long-term outcomes, as well as between treatment characteristics and the avoidance of (ambulatory-care sensitive) rehospitalizations are assessed by using appropriate regression models.

We attempt to describe the heterogeneity in health care utilization among sepsis survivors by Latent Class Analysis (LCA) modelling, which has proven as a promising tool to identify subgroups of patients with different patterns of health service use in previous research [18]. We will assess the stability of the class analysis over the follow-up period and study potential change in latent class membership by latent transition analysis (LTA) [19]. Additional analyses aim at explaining the heterogeneity in health care utilization by individual characteristics of the patients (e.g., age, sex, co-morbidities) and the sepsis (e.g., organ dysfunctions, duration of mechanical ventilation) by including these variables as predictors of the latent class membership in a multinomial logistic regression. Furthermore, the latent class membership may predict short and long-term outcomes, which can also be analyzed using regression based approaches with the latent classes as predictor of distal outcomes as described by Bakk and Kuha [20].

### Module 2: Patient care reports of emergency medical services and health claims data – separate and linked analysis

#### Design and data source

Module 2 is a population-based cohort study formed by patients who are cared for by emergency medical services (EMS) in the two German federal states Bayern (BY) and Baden-Württemberg (BW). In both states, standardized documentation in EMS as well as extensive efforts for quality assurance have existed for quite some time [21].

As first data source, patient care reports (PCR) of rescue drives conducted by paramedics and/or emergency physicians will be acquired from four ground-based EMS organizations. Activities from 29 EMS districts are incorporated. In addition, PCR of one supra-regional air-based EMS organization will be included. In Germany, paramedics can carry out rescue operations independently or in collaboration with emergency physicians. The latter either accompany the operation right from the start or are only called upon if a need arises during the deployment. On the local level, several EMS organizations may operate simultaneously.

As second data source, the statutory health insurance funds AOK BW and AOK BY which have the largest market share in the respective federal states with more than 4 million insured persons each, provide health claims data on the person level. The PCR are linked to health claims data via health insurance number (KVNR) pseudonymized with the widely used SHA-256 algorithm. In case the pseudonymized KVNR of a person is missing, linkage is conducted using indirect key variables following an approach developed by Goldhahn et al. [22] For insured persons for whom a successful linkage is possible, additional health claims data will subsequently be provided by AOK Research Institute WIdO as third data source. The health claims data delivered by WIdO are consistent with the sections of SGB V and XI listed in Module 1. The initial data sources, the linkage process as well as the resulting databases are depicted in Fig. 2.

**Fig. 2 Fig2:**
[figure not shown]
Data sources, linkage and resulting databases in module 2 of AVENIR. Abbreviations: AOK: Statutory Health Insurance Fund, AOK – Die Gesundheitskasse; BY: Bayern, Federal State, BW: Baden-Württemberg, Federal State, EMS: Emergency Medical Services, PCR: Patient Care Report, SGB: Social Code Book, Sozialgesetzbuch, WIdO: AOK Research Institute, Wissenschaftliches Institut der AOK

Module 2 is based on (A) analyses of the PCR and (B) analyses on the linked data (PCR and health-claims data), which allows to trace care pathways and outcomes of sepsis patients from the pre-hospital setting onwards in short as well as long-term.

#### Patient sample

(A) The patient sample includes all EMS cases treated by cooperating EMS organizations in Bayern and Baden-Württemberg between January 1, 2017, and December 31, 2021.

(B) The patient sample consists of individuals for whom a linkage can be established between PCR and health claims data. The health claims data cover the period from January 1, 2016, to December 31, 2022, thereby allowing for a one-year pre- or post-analysis of all patients' EMS-cases. The sample only includes data from individuals with a continuous insurance period or death within observation period.

In module 2, neither PCR nor health claims data are subject to sepsis-specific pre-selection. Consequently, the PCR comprise cases of patients with and without suspected sepsis, and the health claims database consists of patients with and without diagnosed sepsis.

#### Sample size considerations

Due to the varying characteristics of the study regions and EMS- organizations, it is challenging to forecast the number of expected cases. By extrapolating the experience from a research project comparable to AVENIR, [22] we expect approximately 2.8 million PCRs for module 2 (A). Around 40% of the population in the federal states of BY and BW is insured with the AOK. Thus, we estimate approximately 1.1 million cases can be linked to the health claims data for further analyses in (B). Consequently, given a sepsis rate of 2—4% in EMS, [23, 24] around 22.700—45.400 cases of patients with sepsis are to be expected.

#### Measurements

(A) The PCR are first examined with regard to their documentation quality. This includes, for example, the frequency of missing values, invalid values or non-plausible values. Checks of vital signs are especially important in this process, since they are often not documented even in case of suspected infection or sepsis [25].

We will investigate the proportion of patients with a documented suspicion of sepsis in the pre-hospital setting and the symptoms of these patients. We analyze what proportion of patients with suspected sepsis already receive care by emergency physicians in the pre-hospital setting, and how the pre-hospital care of sepsis patients with and without the involvement of emergency physicians differs. In addition, we investigate which therapies are initiated in the pre-hospital setting if sepsis is suspected (e.g., drug administration, oxygen administration, ventilation, administration of antibiotics, fluid therapy, catecholamines, vasopressors).

(B) Based on the linked data, we assess in which sectors (e.g. outpatient treatment, inpatient admission to a hospital) of the health care system patients received follow-up care after EMS treatment, and if this care differs with respect to sepsis suspicion during EMS treatment. Further analysis will determine whether sepsis suspicion in the pre-hospital setting affects short- and long-term patient outcomes (e.g., ventilation, mortality, readmission due to specific diagnoses, need for new care).

In addition, sepsis-specific screening tools such as qSOFA and others [26, 27] will be operationalized based on available vital signs in PCR. The aim is to evaluate how precise the pre-clinical screening tools detect sepsis and if this precision changed over time compared to a clinically confirmed and coded sepsis diagnosis (defined in accordance to Module 1) during a subsequent hospitalization.

A special focus lies on false-negative classifications, i.e. patients without a pre-clinical suspicion of sepsis but confirmed sepsis diagnosis in health claims data. For this group, potential sepsis characteristics (e.g. organ dysfunction by qSOFA) or patient characteristics will be investigated in more detail.

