#### Patient sample

Patients > 15 years of age with hospital-treated sepsis in 2016–2020 are included, as identified by the following strategies based on primary or secondary ICD-10-GM hospital discharge diagnoses (Table 1).

**Table 1 Tab1:** Sepsis definition criteria in health claims data

Year(s)	Sepsis and Infection ICD-10-GM Codes	Organ dysfunction ICD-10-GM or OPS Codes
2016–2019	R57.2 (septic shock) OR	
	R65.1 (severe sepsis) OR	
	At least one explicit sepsis code (A02.1, A20.0, A20.7, A21.7, A22.7, A24.1, A26.7, A28.2, A32.7, A39.1, A39.2, A39.3, A39.4, A40, A41, A42.7, A48.3, A49.9, A54.8, B00.7, B37.6, B37.7, B49, O75.3, O85, T80.2, T81.4, T88.0)	AND at least one ICD-10-GM code for organ dysfunction (J80.0, J95.1, J95.2, J96.0, J96.9, R09.2, D65, D69.57, D69.58, D69.59, D69.6, R57.8, E86, I95.9, I46.0, I46.9, R57.2, K72.0, K72.9, R17, N17.02, N17.03, N17.12, N17.13, N17.22, N17.23, N17.82, N17.83, N17.92, N17.93, F05, G94.32, K72.72!, K72.73!, K72.74!, R40, G93.4) OR OPS code for organ dysfunction (8–701,^a^ 8–704,^a^ 8–706,^a^ 5–311,^a^ 5–312,^a^ 8–800.6, 8–800.d, 8–800.f, 8–800.g, 8–800.h, 8–800.j, 8–800.k, 8–800.m, 8–800.n, 8–810.j, 8–810.x, 8 812.5, 8–812.6, 8–812.8, 8–771, 8–779, 8–852, 8–858, 8–821.2, 8–853.1, 8–853.3, 8–853.4, 8–853.5, 8–853.6, 8–853.7, 8–853.8, 8–853.x, 8–853.y, 8–854.2, 8–854.3, 8–854.4, 8–854.5, 8–854.6, 8–854.7, 8–854.8, 8–854.x, 8–854.y, 8–855.1, 8–855.3, 8–855.4, 8–855.5, 8–855.6, 8–855.7, 8–855.8, 8–855.x, 8–855.y, 8–856, 8-85a.0, 8-85a.1)
2020	R57.2 (septic shock) OR	
	At least one explicit sepsis code (see above)	AND R65.1 (SIRS with organ dysfunction) OR
	At least one explicit sepsis code (see above)	AND at least one ICD-10-GM code for organ dysfunction (see above) OR OPS code for organ dysfunction (see above) OR
	J09 OR J10 (laboratory confirmed Influenza) OR U07.1! (laboratory confirmed SARS-CoV2-infection)	AND at least one ICD-10-GM OR OPS code for organ dysfunction (see above)

*Abbreviations*: *ICD-10* International Classification of Diseases Version 10, German Modification, *OPS* German Procedure Classification, Operationen- und Prozedurenschlüssel

^a^codes were included in the definition if at least one hour of mechanical ventilation was documented in the course of the hospitalization

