ICD-10-GM for sepsis codes were consistently defined by sepsis-1 definition [15] until the end of 2019. In 2020, sepsis coding was adjusted to the new sepsis-3 definitions [1]. To address these changes and to capture patients with viral sepsis, for which no explicit sepsis code is available since the change of the definitions, we extended our case identification strategies to cases with a code for Covid-19 or Influenza and a code indicating an acute organ dysfunction. The first hospital case of a patient with sepsis in the observation period is referred to as the index treatment; possible following sepsis cases are considered as recurrent sepsis. Only patients with continuous insured status 12 months before and 24 months (12 months for the 2020 patient cohort) after index treatment with sepsis or until death are included in the study.

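### Change in screening-tool accuracy over 2017–2021 is judged against a reference definition that changes between 2019 and 2020 and has no rule for 2021, so a difference across that boundary cannot be attributed to the tools or to EMS practice

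*Protocol article*

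**What the plan says.** Module 2, Measurements (B), sets the aim. Tools such as qSOFA are built from the vital signs in the patient care reports (PCR) and compared with coded sepsis in a later hospital stay. One question is "if this precision changed over time compared to a clinically confirmed and coded sepsis diagnosis (defined in accordance to Module 1"). Module 2, Statistical analyses, names sensitivity, specificity and the predictive values as the measures.

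The EMS cases are those treated "between January 1, 2017, and December 31, 2021" (Module 2, Patient sample). For the linked claims, "The health claims data cover the period from January 1, 2016, to December 31, 2022".

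The definition referred to is in Module 1, Patient sample: "Patients > 15 years of age with hospital-treated sepsis in 2016–2020 are included". Its Table 1 has two rows.

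- In 2016–2019, one of the qualifying entries is "R65.1 (severe sepsis) OR", so that code is enough alone.
- In 2020 the code appears only next to an explicit sepsis code: "AND R65.1 (SIRS with organ dysfunction) OR". A new route is added, "J09 OR J10 (laboratory confirmed Influenza) OR U07.1! (laboratory confirmed SARS-CoV2-infection"), which needs an organ-dysfunction code but no sepsis code.

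The text below the table adds that "In 2020, sepsis coding was adjusted to the new sepsis-3 definitions", after sepsis-1 coding up to the end of 2019. Table 1 has no row after 2020.

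**The concern.** A comparison of diagnostic accuracy over time needs a reference standard that means the same thing at each point. Here three things happen inside the window: the case rule changes, the national coding basis changes, and the rule stops a year before the EMS data do.

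Taken literally, Table 1 makes an influenza patient with an organ-dysfunction code, but no sepsis code, R65.1 or R57.2, reference-negative in 2019 and reference-positive in 2020. The vital signs and the tool score could be identical. A shift in measured accuracy at 2020 could then be read as tools or crews getting better or worse when only the reference moved. For 2021 the article does not say which cases count as sepsis, which affects every accuracy estimate for that year and not only the trend.

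**Working it through.** **The rules by EMS year**

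| EMS years | Coding basis | R65.1 without a sepsis code | Influenza or Covid-19 plus organ dysfunction, no sepsis code |
|---|---|---|---|
| 2017–2019 | sepsis-1 | counts | does not count |
| 2020 | sepsis-3 | does not count | counts |
| 2021 | sepsis-3 presumed to continue | no rule given | no rule given |

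Three EMS years fall under the first rule, one under the second and one under none.

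**The plan's own figure.** Module 2, Sample size considerations, gives 2.8 million PCRs, an AOK share of about 40% and a sepsis rate of 2–4%.

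- 2.8 million × 0.40 = 1.12 million (stated: about 1.1 million).
- 1.12 million × 0.02 = 22,400 and × 0.04 = 44,800 (stated: 22,700 and 45,400).
- The stated range implies a base of 22,700 / 0.02 = 1.135 million, which is 40.5% of 2.8 million. The 1.3% gap is rounding, and the figure reproduces.

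**Cases per year, assuming an even spread**

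- Linked cases: 1.1 million / 5 = 220,000.
- Sepsis cases: 22,700 / 5 = 4,540 to 45,400 / 5 = 9,080.

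**How far the reference change alone could move the results.** The document gives none of the inputs needed, so the following are assumptions: tool sensitivity 50% in sepsis meeting the 2016–2019 rule, false-positive rate 10%, prevalence 2–4%, added viral cases equal to 10–30% of the other cases, tool sensitivity 30–70% in those viral cases, and 0–10% of cases lost because R65.1 alone no longer counts. Tool and patients are held fixed; only the rule changes.

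- Sensitivity = [(C − D) × s + V × s_v] / (C − D + V), where C is cases under the old rule, D cases lost, V viral cases added, and s and s_v the two sensitivities.
- Extremes, with C = 1, D = 0.1, V = 0.3: for s_v = 0.3, (0.45 + 0.09) / 1.2 = 45%; for s_v = 0.7, (0.45 + 0.21) / 1.2 = 55%.
- If s_v = s, sensitivity stays at 50%.
- At 4% prevalence, positive predictive value (PPV) starts at 16–17% and ends between 16.4% and 23.1%. The upper end, per 1,000 linked cases with C = 40, V = 12, D = 0, s_v = 0.7: true positives 20 + 8.4 = 28.4; false positives 948 × 0.10 = 94.8; PPV = 28.4 / 123.2 = 23.1%. Under the old rule it is 20 / 123.2 = 16.2%.
- At 2% prevalence, PPV starts at about 9% and ends between 8.9% and 12.7%.

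**Would such a shift show?** The smallest year-to-year difference in sensitivity detectable with 80% power at two-sided 5%, near 50%, is (1.960 + 0.842) × √(2 × 0.25 / n). This is 2.9 points for n = 4,540 and 2.1 points for n = 9,080. Missing vital signs would reduce n and raise these values. A shift of up to 5 points from the definition alone could look like a clear trend.

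**The case against.** The strongest reply is that the two rows bridge a coding change the authors did not control. Module 1, Patient sample, explains that the viral route was added because viral sepsis has had no explicit code since the definitions changed. This implies that such patients could carry one before. On that reading, removing the route would create a break of its own. The Discussion also names the 2020 code change as a limitation and offers the two strategies as the response. Further, the Project timeline says analysis plans for Modules 1 and 2 were prepared; they are not shown and may split results at 2020. Table 1 stops at 2020 because Module 1's cohort does, and carrying the latest rule forward is the natural reading.

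Much of this stands. The viral route is not a mistake, and a common code set is not a cure. But the Discussion treats the code change as a problem of capturing cases and does not mention the comparison over time. Nor does the point rest on an omitted detail: the article itself fixes the reference by pointing to a definition that changes mid-window and ends a year early. The pathogen subgroups promised in Module 1, Measurements, are for Module 1 analyses.

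A reader might infer that no real trend can be recovered at all. The document does not support that: within 2017–2019 the rule and the coding basis are constant. A reader might also infer that sensitivity, specificity and both predictive values must all shift. They need not: sensitivity does not move if the tool performs equally in viral and other sepsis.

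**Conclusion.** The point holds for comparisons across the 2019/2020 boundary and for 2021. Followed as written, a difference in accuracy across that boundary cannot be attributed to the tools or to EMS practice, because the case rule and the coding basis both change there. Trends within 2017–2019 stand.

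About 220,000 linked cases a year are involved if they are evenly spread, and 2021 is about one fifth of the linked data. Sizing this on all PCRs (2.8 million / 5 = 560,000 a year) might be tempting, but accuracy is assessed only in the linked data. The shift of up to 5 points in sensitivity is an illustration under stated assumptions and not an estimate. Module 1, Sample size considerations, expects Covid-19 cases to keep the 2020 cohort at a similar size, but gives no viral share.

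The date of the switch is read from the calendar-year rows of Table 1 and the statement that sepsis-1 coding ran to the end of 2019. The consequence is limited to this one aim and the 2021 accuracy estimates; data collection and linkage are unaffected.

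**What to change.** In Module 2:

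1. State that the 2020 rule applies to 2021 EMS cases and to their hospital stays ending in 2022.
2. Report and interpret accuracy over time separately for 2017–2019 and 2020–2021, and claim no trend across the boundary.
3. Report 2020–2021 accuracy with and without the Covid-19/influenza route.
4. Add a sensitivity analysis with one common code set in all years: R57.2, or an explicit sepsis code plus either R65.1 or an organ-dysfunction code. Say that it does not remove the sepsis-1 to sepsis-3 coding change and may lose viral sepsis differently before and after 2020.

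The cost is a little more analysis, using codes already listed in Table 1. The sensitivity analysis will have fewer reference-positive cases, possibly by a substantial share from 2020, and it also drops the cases with R65.1 alone from 2017–2019. The study gives up a single five-year trend.

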#### Statistical analyses

Data quality in the PCR is primarily examined with an exploratory approach. We plan to use methods for the assessment of data quality (e.g. visualization through heat maps). For analyses in (A) and (B) we use frequency counts, cross-tabulations, measures of location and dispersion measures.

The characteristics of pre-clinical sepsis screening tools are analyzed by using binary classifiers. Measures such as sensitivity, specificity, negative/positive predictive value, are calculated.

Additionally, descriptive measures and appropriate visualization techniques, such as Sankey plots, are utilized to depict pre-hospital patient pathways, including emergency care, inpatient admission or utilization of other health care sectors. This is performed for the total patient sample, but also for subgroups (e.g., by age, gender, comorbidity). In order to evaluate acute and long-term patient outcomes, module 2 employs descriptive and multivariate analysis methods, which are suitable for the data structure. Survival times of patients are investigated by using the Kaplan–Meier estimator.

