Our study has also limitations to consider. On the one hand, these arise from inherent limitations of research using health claims data, such as potentially incomplete, inaccurate, or missing data, and inability to adequately evaluate the appropriateness of care [37, 38]. Although health care utilization and costs can be researched with high validity, recorded incidences of diseases have to be considered as administrative as only diseases diagnosed and coded correctly during hospitalizations and outpatients visits can be detected. For sepsis, we know from previous validation studies that the coding of diagnoses captures cases only with low sensitivity, and misses cases with lower disease severity [39]. This fact may be aggravated by the change in sepsis-related ICD-10-GM codes in 2020 in Germany. We address this issue by applying different case identification strategies for the years 2016–19 and 2020 (Table 1), but still it is likely that our sepsis definition does not capture all sepsis patients treated in German hospitals.

In module 2, exclusively PCR of EMS from study regions in Bayern and Baden-Württemberg as well as from selected EMS organizations will be processed. Hence, all generalizations of study results with regard to these two federal states or to the entire health care system in Germany must be examined carefully.

Furthermore, undesired selection effects may be introduced into the database in case key variables needed for the linkage of PCR and health claims data are unavailable selectively (e.g. KVNR). However, it is known from previous studies [22] that data linkage with health claims data is possible even if the key variable KVNR is not available for some of the PCR.

Qualitative data curation in module 3 might be limited by the fact that since participants of the oral interviews are not sharing statements anonymously in interviews and SOFGs, statements might not be free from social desirability effects. The sample might be subject to self-selection bias as participation will be voluntarily. Moreover, interviews using a video conference system may not reach the same depth as face-to-face interviews as rapport building can be limited. However, using online video-supported interviews allow for a composition of groups without logistic concerns and geographical restrictions, which increases the groups ‘ diversity and quality.

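### Module 2 scores screening tools and missed sepsis against discharge coding that the protocol itself calls insensitive, so PPV is very likely understated and the other measures carry an unquantified error

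*Protocol article*

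**What the plan says.** Module 2, Measurements (B), sets the reference for the screening tools: their precision is assessed "compared to a clinically confirmed and coded sepsis diagnosis (defined in accordance to Module 1) during a subsequent hospitalization". The same section gives special attention to false negatives, defined as "patients without a pre-clinical suspicion of sepsis but confirmed sepsis diagnosis in health claims data". Module 2, Statistical analyses, then states: "Measures such as sensitivity, specificity, negative/positive predictive value, are calculated".

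The definition being borrowed is in Module 1, Patient sample and Table 1. Patients are included "as identified by the following strategies based on primary or secondary ICD-10-GM hospital discharge diagnoses", with ICD or procedure codes supplying the organ dysfunction. No chart review or adjudication is described.

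The limitations paragraph of the Discussion reports from earlier validation work that "the coding of diagnoses captures cases only with low sensitivity, and misses cases with lower disease severity". It adds that, even with separate definitions for 2016-2019 and 2020, "it is likely that our sepsis definition does not capture all sepsis patients treated in German hospitals". Among the strengths, the same Discussion lists the ability to explore how much sepsis goes unrecognised in EMS care.

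**The concern.** The reference standard is an administrative record, yet it is labelled as clinical confirmation. The protocol's own statement about its accuracy stops at case capture and does not reach the quantities that depend on it most.

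Two misclassifications follow. A septic patient who is flagged before hospital but never coded is scored as a false positive. A septic patient who is neither flagged nor coded is scored as a true negative, although that patient is exactly what unrecognised sepsis means. Because the uncoded cases are said to be the milder ones, the coded cases are also not a fair sample of sepsis on which to measure detection.

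At stake is how the results are read. Tools could appear to raise many more false alarms than they do, and the number of missed cases could be wrong in a direction the plan does not examine. Module 2 also asks whether precision changed over time. The Discussion says the 2020 coding change may worsen under-capture, so a shift in the reference could look like a shift in the tools.

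**Working it through.** **1. The plan's own figure.** Module 2, Sample size considerations, expects 2.8 million patient care reports and states: "Around 40% of the population in the federal states of BY and BW is insured with the AOK". 2.8 million × 0.40 = 1.12 million linked cases. At its 2-4% sepsis rate this gives 22,400 to 44,800, against the stated 22,700 to 45,400 (about 1.3% higher, which would need 1.135 million). The figure reproduces adequately. N = 1.12 million is used below.

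**2. Assumptions.** The protocol gives no number for coding accuracy or tool accuracy. The 2-4% is taken as true prevalence.
- Scenario A: half of sepsis severe; coding sensitivity 50% severe, 20% mild (35% overall); tool sensitivity 70% severe, 40% mild; tool specificity 85%.
- Scenario B: as A, but coding sensitivity 35% regardless of severity.
- Scenario C: 30% severe; coding sensitivity 60% severe, 10% mild (25% overall); tool sensitivity 80% severe, 30% mild; tool specificity 85%.
- No false-positive coding in any of them at first.

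**3. Scenario A at 2%.**
- Sepsis 22,400 (11,200 severe, 11,200 mild); no sepsis 1,097,600.
- Flagged sepsis: 11,200 × 0.70 + 11,200 × 0.40 = 12,320. Flagged without sepsis: 1,097,600 × 0.15 = 164,640. All flagged: 176,960.
- Coded: 11,200 × 0.50 + 11,200 × 0.20 = 7,840. Coded and flagged: 11,200 × 0.50 × 0.70 + 11,200 × 0.20 × 0.40 = 4,816.
- PPV: true 12,320 / 176,960 = 6.96%; apparent 4,816 / 176,960 = 2.72%.
- Tool-negative sepsis: true 22,400 − 12,320 = 10,080; apparent 7,840 − 4,816 = 3,024.
- Sensitivity: true 12,320 / 22,400 = 55.0%; apparent 4,816 / 7,840 = 61.4%.
- Specificity: true 85.0%; apparent 1 − (176,960 − 4,816) / (1,120,000 − 7,840) = 84.5%.
- NPV: unflagged 1,120,000 − 176,960 = 943,040; true 1 − 10,080 / 943,040 = 98.93%; apparent 1 − 3,024 / 943,040 = 99.68%.

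At 4% the same steps give specificity 84.0% against 85.0% and NPV 99.35% against 97.84%.

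**4. Range (apparent vs true).**

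| Scenario | Prevalence | PPV | Sensitivity | Tool-negative sepsis |
|---|---|---|---|---|
| A | 2% | 2.72% vs 6.96% | 61.4% vs 55.0% | 3,024 vs 10,080 |
| A | 4% | 5.18% vs 13.25% | 61.4% vs 55.0% | 6,048 vs 20,160 |
| B | 2% | 2.44% vs 6.96% | 55.0% vs 55.0% | 3,528 vs 10,080 |
| B | 4% | 4.64% vs 13.25% | 55.0% vs 55.0% | 7,056 vs 20,160 |
| C | 2% | 2.12% vs 5.77% | 66.0% vs 45.0% | 1,904 vs 12,320 |
| C | 4% | 4.07% vs 11.11% | 66.0% vs 45.0% | 3,808 vs 24,640 |

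**5. How much false-positive coding reverses each direction.** Scenario A at 2%, with x non-septic contacts wrongly coded and flagged at the same 15% rate:
- Sensitivity: (4,816 + 0.15x) / (7,840 + x) = 0.55 gives x = 1,260, or 0.11% of 1,097,600. At 4%: 2,520, or 0.23%.
- Missed count and NPV: 3,024 + 0.85x = 10,080 gives x = 8,301, or 0.76% (coding specificity 99.24%). At 4%: 16,602, or 1.54% (98.46%).
- PPV: 4,816 + 0.15x = 12,320 gives x = 50,027, or 4.6%. That exceeds the plan's whole expected sepsis count.

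The PPV threshold depends on wrong coding being unrelated to the tool result. In the extreme where every wrongly coded contact had been flagged, 4,816 + x = 12,320 gives x = 7,504 (0.68%). Even then 7,504 / (7,504 + 7,840) = 49% of all coded cases would have to be wrong.

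**The case against.** **The limitation is disclosed, and the reference is stated to be coded.** The Discussion calls recorded diagnoses administrative, and throughout the protocol clinical often just means in hospital, so the label can be read as diagnosed in hospital and coded. This softens the wording point. It does not remove it: nothing beyond codes confirms the diagnosis, and the disclosure is never connected to the accuracy measures or the false-negative group.

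**Analysis plans exist.** Project timeline says they were prepared for Modules 1 and 2, and a bias analysis might be there. That is fair, and its absence from an article would not be a finding by itself. The point here is what the article does fix: a reference, a label for it, and a contrary statement about its accuracy.

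**The direction of error is not known for every measure.** A reader might infer that PPV and specificity are understated and that sensitivity and NPV are overstated, all without conditions. The documents do not support that. They give no coding specificity, and from 2020 a Covid-19 or influenza code plus any listed organ-dysfunction code counts as sepsis, which could admit false positives. Module 2 also does not restrict the later coded sepsis to community-acquired cases, although Module 1 does so for its pre-hospital analysis. Sepsis acquired after admission would be scored as missed, which lowers apparent sensitivity and inflates the missed count. This objection stands.

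**Tool and crew differ.** The special-focus group is defined by absence of pre-hospital suspicion, not by a tool result. The counts above are for a tool and do not size that group, although the same mechanism applies to it.

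**Conclusion.** The point holds in a conditional form. The reference is discharge coding, the protocol says it is insensitive and misses milder cases, and the planned measures would be reported as tool accuracy without that error.

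- **PPV:** very likely understated. Apparent PPV is about 35-39% of the true value across the three scenarios. Reversal in scenario A at 2% needs about 4.6% of non-septic contacts wrongly coded, if wrong coding is unrelated to the tool result.
- **Missed sepsis and NPV:** undercounted and overstated respectively, but only if coding specificity is above about 99.2% (2% prevalence) or 98.5% (4%) and hospital-acquired sepsis does not dominate.
- **Sensitivity:** direction uncertain. There is no bias if coding misses cases regardless of severity, and in scenario A the bias reverses at 0.1-0.2% false-positive coding.
- **Specificity:** about 0.5-1 point in scenario A, which is of little practical weight.

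All sizes rest on assumed coding and tool accuracy. A reader might also take the 2-4% as the rate of coded sepsis and scale it up, which would produce larger contrasts. The protocol calls it a sepsis rate in EMS, so that reading is not supported. The change is worth making, but the point does not undermine the rest of Module 2.

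**What to change.** Call the reference claims-coded sepsis wherever Module 2 uses it, and report the tool results as agreement with coded sepsis. Add a bias analysis that recomputes sensitivity, specificity, PPV, NPV and the missed-sepsis share over a stated range of both coding sensitivity and coding specificity, allowing lower detection in uncoded, milder cases. Do this separately for the tools and for crew suspicion. Extend the Discussion's limitation by a sentence saying that the accuracy measures and the extent of unrecognised sepsis inherit it.

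A broader claims reference (any infection code plus organ dysfunction, as Table 1 already does for Covid-19 and influenza) could be shown as a secondary analysis only. It is less specific and exchanges one unknown error for another.

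No new data are needed. The cost is some wording, a modest amount of extra analysis, and accuracy figures that appear as ranges instead of single values.
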